#### Main cause of complication/death

classification of the determinant main cause of the complication identified among cases and/or the main cause of death.

#### Maternal death

Death of a woman during pregnancy or within a 42-day period following the end of pregnancy irrespective of the duration or localization of the pregnancy, resulting from any cause related to or aggravated by the pregnancy or by measures taken with respect to it; however, not from accidental or incidental causes.

#### Conditions at birth

Vital status of the newborn infant as recorded on the medical chart, dichotomized into live or intrauterine death.

#### Vitality of the newborn infant

Evaluation of the newborn infant according to 1^st ^and 5^th ^minute Apgar scores as shown on the medical chart, classified from 0 to 10.

#### Neonatal outcome

Condition of the newborn infant at the time of data collection, identified from a review of the medical charts and classified as: discharged from hospital together with the mother, early neonatal death (<7 days) or late neonatal death (7-28 days).

#### Quality of life

The woman's perception of her position in life within the cultural context and value system in which she lives and in relation to her goals, expectations, health, standards and concerns (WHO); identified by the investigators using a standard SF-36 form.

#### Posttraumatic stress

Symptoms of intrusion, avoidance and hyperarousal following the occurrence of a pregnancy with severe complications; identified by the investigator using a standard questionnaire (PTSD - Checklist CV).

#### Ideal number of children

Number of children that the woman considered ideal prior to and following the index pregnancy.

#### Return to sexual activity

Time taken by the woman to recommence sexual activity after delivery and reason given for not recommencing sexual activity.

#### Sexual function

Sexual function and response; identified by the investigator using a standard questionnaire (*Female Sexual Function Index - FSFI*).

#### Postpartum depression

Depressive symptoms following the occurrence of a pregnancy with severe complications; identified by the investigator using a standard questionnaire (Edinburgh Postnatal Depression Scale - EPDS).

#### Functional status

Perception of the woman with respect to her functional status in six items related to her routine activities (understanding and communicating, getting around, self-care, getting along with people, life activities in the home/at work and participation in society), classified from 0 to 100 (from best to worst) [25].

#### Neuromotor development in the child born from the index pregnancy

Process of changes in motor behavior that involve both maturation of the central nervous system and interaction with the environment and stimuli given during the child's development; identified by the investigator using the Denver II - Revised Denver Developmental Screening Test [26].

#### Weight-height development of the child born from the index pregnancy

Process of weight and height increment during the child's development, weight measured in grams and height in centimeters, using scales and anthropometer, classified as adequate or inadequate for age, according to the standards of the World Health Organization [27].

#### Control variables

maternal age, marital status, place of residence, number of previous pregnancies, parity, previous abortions, previous Cesarean sections, number of children, mode of delivery, gestational age, birthweight, gender of neonate, condition of neonate at discharge, condition of mother at discharge.

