### Main hypotheses

In survivors of severe acute maternal morbidity:

• health and quality of life would be poorer;

• posttraumatic stress would be more common;

• postpartum depression would be more common;

• sexual function would have deteriorated and the woman's return to sexual activity would take longer;

• functional status in routine activities would be evaluated as poorer.

In the children born from a pregnancy associated with severe maternal morbidity:

• immediate perinatal outcome would be poorer;

• the occurrence of impaired neuromotor and weight-height development would be significantly higher.

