For the multidimensional analysis of the repercussions of severe maternal morbidity, a concurrent cohort, specific population study will be carried out with an externally selected comparison group. The main exposure factor will be the occurrence of severe maternal morbidity (both maternal potentially life threatening or near miss conditions). During the second half of the cross-sectional study, a sample of women identified as having severe maternal morbidity will be selected and invited to participate in the longitudinal evaluation. There will be a comparison group composed of women who did not suffer severe maternal morbidity. These women will be randomly selected externally in a proportion of 1:1 from postpartum women in the rooming-in wards of the same maternity hospitals as the cases. Controls will be selected at random and balanced according to mode of delivery, maternal age and gestational age at the time of delivery.

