### Data Collection and Procedures

#### Cross-sectional component

Research assistants, referred to as local coordinators, will review the charts of hospitalized patients on a daily basis in search of cases with one of the conditions identifying severity (Appendix 2). In cases found with these diagnoses, the relevant hospital records will be reviewed for data collection following the women's hospital discharge, death or transfer to another healthcare facility. Data unavailable on the chart but of interest to the study will be obtained from the attending medical team. For each case included, data will be collected on the demographic and obstetric characteristics of the patient, the primary determinant of maternal near-miss (the first complication to occur in the chain of events leading to severe maternal morbidity), the duration of hospitalization (prior to delivery, following delivery and total time), the occurrence of indicators of maternal near-miss at any time during hospitalization, indicators of perinatal outcome and conditions of the woman at discharge from hospital.

These data will be collected on a previously coded form developed specifically for this purpose. A central database will be constructed and the data will be included by the local investigators themselves using electronic forms. The manually completed forms will be filed and made available at technical visits for the purpose of quality control.

For the electronic inclusion of data, each center will have its own restricted area on the study website where password-protected access will be granted only to cases included at that center. An overview of all the cases included in the network will be provided in the form of monthly graphs and tables containing the number of cases included by each center. In addition, the reported diagnoses will be provided by the coordinating center on the main page of the website.

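### The control-variable list holds no previous mental illness, schooling or income, and the cohort records no pre-event state, so differences in maternal mental health and quality of life cannot be separated from pre-existing ones

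*Protocol article*

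**What the plan says.** All references are to the protocol article.

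- **Control variables.** One list serves the whole study. Its first seven items are "maternal age, marital status, place of residence, number of previous pregnancies, parity, previous abortions, previous Cesarean sections". The other seven are "number of children, mode of delivery, gestational age, birthweight, gender of neonate, condition of neonate at discharge, condition of mother at discharge". The list has no open-ended wording.
- **Methods/Design (cohort paragraph).** "The main exposure factor will be the occurrence of severe maternal morbidity", so the comparison is observational. Controls are "randomly selected externally in a proportion of 1:1 from postpartum women in the rooming-in wards of the same maternity hospitals as the cases". On balance, "Controls will be selected at random and balanced according to mode of delivery, maternal age and gestational age at the time of delivery". The Longitudinal component section repeats these three factors and adds that eligible controls are admitted on the same day as the case.
- **Longitudinal component.** Quality of life and postpartum depression are first asked about by telephone at 3 months and again at 6 months. Posttraumatic stress, sexual function and functional status are first measured at the 6-month visit. The in-hospital contact is described for invitation, consent and scheduling only.
- **Main hypotheses.** In survivors, "posttraumatic stress would be more common", with parallel hypotheses for depression, quality of life, sexual function and functional status.
- **Data analysis.** Relative risks are planned for these outcomes, two of them worded as a deterioration. No adjusted estimate is specified.
- **Cross-sectional component.** For each case, "data will be collected on the demographic and obstetric characteristics of the patient". The items are not listed, and nothing says the same is done for cohort controls.

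**The concern.** The outcomes at issue are depression, posttraumatic stress, sexual function, quality of life and functional status. All of them can be impaired before pregnancy. If women with severe morbidity differ from controls in psychiatric history or social position, part or all of an observed excess may have been present before the event. The design offers three places to deal with this: control selection, a baseline measurement, and covariates. None of the three, as described, captures psychiatric history, schooling or income.

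At stake are the cohort's main maternal hypotheses. From what the article describes, a later analysis could not repair the gap, because adjustment needs the same information from both groups and no described step collects it.

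The list also puts variables that follow the exposure, such as birthweight and "condition of neonate at discharge, condition of mother at discharge", under the same label as true pre-event characteristics. Adjusting a maternal outcome for these could remove part of the effect under study while the pre-event difference stays in.

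**Working it through.** **Step 1: item check of the list.** The 14 items fall into three groups.

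| Group | Items |
|---|---|
| Sociodemographic (3) | maternal age, marital status, residence |
| Obstetric and family history (5) | pregnancies, parity, abortions, Cesareans, number of children |
| Index delivery and after (6) | mode of delivery, gestational age, birthweight, neonatal sex, discharge condition of neonate, discharge condition of mother |

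Psychiatric history, schooling and income are absent here, and no other section names them as covariates.

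**Step 2: can another part of the design stand in?**

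- *Control selection.* It balances mode of delivery, maternal age and gestational age. Same-hospital, same-day recruitment may partly equalise catchment and so social position. It gives no reason to expect balance in psychiatric history.
- *Baseline measurement.* None is described. The PTSD checklist asks about symptoms over the past month, so symptoms that predate the pregnancy and persist would count.
- *Analysis.* Relative risks are named without further protection. A deterioration is a change from an earlier state, and no earlier state is recorded for these outcomes.

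**Step 3: possible size.** The plan gives no figure on this point, so there is none to reproduce. All inputs below are assumptions:

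- p1 = previous depression in exposed women, 15-25%
- p0 = previous depression in controls, 10-15%
- r = factor by which it multiplies the risk of postpartum depression, 2-4

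With no true effect of the exposure, and the same r in both groups, the spurious relative risk is

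B = [1 + p1(r - 1)] / [1 + p0(r - 1)].

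| p1 | p0 | r = 2 | r = 3 | r = 4 |
|---|---|---|---|---|
| 15% | 15% | 1.15/1.15 = 1.00 | 1.30/1.30 = 1.00 | 1.45/1.45 = 1.00 |
| 15% | 10% | 1.15/1.10 = 1.05 | 1.30/1.20 = 1.08 | 1.45/1.30 = 1.12 |
| 25% | 15% | 1.25/1.15 = 1.09 | 1.50/1.30 = 1.15 | 1.75/1.45 = 1.21 |
| 25% | 10% | 1.25/1.10 = 1.14 | 1.50/1.20 = 1.25 | 1.75/1.30 = 1.35 |

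The assumed ranges therefore give 1.00 to 1.35. Equal prevalence gives no bias, and a lower prevalence in exposed women would push the factor below 1. The calculation covers one binary confounder of one binary outcome. Nothing is computed for schooling, income or the other outcomes.

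**The case against.** The strongest reply is that this is a condensed article. The list does not say it is exhaustive, no model is named, and the data form and operations manual are not shown. Schooling could sit among the demographic data. The Ethical aspects section mentions women who already have a diagnosis, so some history may be elicited. Same-hospital, same-day controls may share much of the cases' social background.

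Part of this stands. The social imbalance may be smaller than it would be with population controls, and the form may hold more than the article shows. It does not remove the point. The article states an itemised list instead of leaving the matter open. The demographic data are described for cross-sectional cases only. The remark on existing diagnoses concerns referral for care and not a covariate. Nothing shown yields psychiatric history or a socioeconomic measure for both groups.

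A reader might also infer four stronger things that the document does not support:

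- *The list was drawn up for the mental-health hypotheses and holds only obstetric and post-event items.* It is study-wide, also serves perinatal and infant outcomes, and includes age, marital status and residence.
- *The plan will adjust maternal outcomes for post-event variables.* Data analysis specifies no adjusted relative risk. The fault is that the list does not separate such variables from pre-event ones.
- *The omitted variables are the main causes of these outcomes.* That is a subject-matter judgement on which the document gives no figures.
- *A bias is demonstrated.* It depends on a difference between the groups that is assumed here, and the assumed range includes no bias.

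**Conclusion.** The point holds as a correctable gap in the cohort's design. Followed as written, the plan cannot separate an effect of severe morbidity on the maternal outcomes from a pre-existing difference in mental health or social position. That conclusion rests on the stated list, the three balancing factors and the absence of any described pre-event measurement.

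The size of any bias is unknown. The range of 1.00 to 1.35 illustrates what assumed prevalences and risk multipliers would produce and does not estimate what this study will see. The document's Background links better social conditions to lower maternal mortality, which makes some social difference between the groups plausible but does not quantify it. A spurious relative risk near the upper end could be mistaken for support of a main hypothesis, so the change is worth making before cohort enrolment.

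**What to change.** 1. **Add to Control variables, and collect from both groups:** previous diagnosis or treatment for depression, anxiety or PTSD; years of schooling; household income or an equivalent measure.
2. **Ask at the in-hospital consent contact.** The 3-month call is a poorer place, because the depression questionnaire is given in that call and current mood could colour recall. A retrospective item is in keeping with this study, which already records the number of children considered ideal before the index pregnancy.
3. **In Data analysis,** report relative risks for the maternal cohort outcomes adjusted for these items, beside the crude ones.
4. **For those maternal outcomes only,** do not adjust the main estimate for birthweight or for the discharge condition of mother or neonate, which can result from the exposure. Keep the balancing factors (mode of delivery, maternal age, gestational age) and leave the infant-outcome analyses as they are.
5. **Wording.** Unless a pre-event state is recorded, describe quality of life, sexual function and functional status as differences between groups and not as deterioration.

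**Cost.** A few extra enrolment questions in both groups. Self-reported history carries error, and it would be taken after the event, so exposed women may recall differently. Adjustment would reduce the confounding but not abolish it.

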#### Longitudinal component

As in the cross-sectional component, women with one of the conditions indicative of severity will be selected as potential subjects for longitudinal evaluation. Once identified, research assistants who are not involved in the cross-sectional portion of the study will invite eligible women to participate in the longitudinal evaluation of the study. Women who agree to take part will be asked to sign an informed consent form and two CATI (computer assisted telephone interview) will be scheduled for 3 and 6 months postpartum plus a medical visit with the woman and the newborn infant six months following delivery.

For the control group, all women admitted to the hospital for obstetric care in the same facility on the same day on which a case has been identified and who have none of the conditions indicating severity will be eligible. Following a process of randomized selection balanced according to mode of delivery, maternal age and gestational age at the time of delivery, women in the control group will be invited to participate in the study by the research assistants in the same way as candidates to the study group. Three months after delivery, the study call center will contact the women to carry out the first step in data collection. At the time of this contact, the interviewers will again go over the objectives of the study and will apply standard questionnaires designed to investigate quality of life and postpartum depression. This interview is estimated to last around 20 minutes.

At six months postpartum, the study call center will contact the women again to carry out the second step in data collection. At this contact, the interviewers will go over the study objectives once again and apply the same standard questionnaires on quality of life and postpartum depression, lasting no more than 20 minutes. In the case of women who do not have a telephone, a reminder letter will be sent asking them to phone the study call center at the sixth month postpartum to enable the interview to take place.

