### Data analysis

Data analysis will be performed in sub-groups according to the time of occurrence of the near-miss or severe maternal morbidity (in adolescence, older ages or at another time in the woman's reproductive life) and determining cause (hypertension, hemorrhage, abortion or other causes). The rates of maternal near-miss will be calculated for each collaborating center using the WHO maternal near miss approach [5], and frequencies of non-near-miss severe maternal morbidity will be calculated using specific defined diagnoses. General estimates will be calculated together with their respective 95% confidence intervals. The association between organ dysfunction and maternal death will be estimated using odds ratios, likelihood ratio test and their respective 95% confidence intervals. In addition, relative risks will be calculated for sexual dysfunction, postpartum depression, posttraumatic stress disorder, deterioration in quality of life, deterioration in the woman's perception of her own functional status in routine activities, risk of adverse perinatal outcome and risk of impaired neuromotor and weight-height development in the children born from the pregnancy associated with severe maternal morbidity.

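### Number of fetuses is missing from the listed control variables and from the balancing of controls, so the infant relative risks can be confounded by multiple pregnancy

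*Protocol article*

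**What the plan says.** Under Main outcomes, the Control variables entry lists 14 items. They include "number of previous pregnancies, parity, previous abortions, previous Cesarean sections, number of children, mode of delivery, gestational age, birthweight, gender of neonate", together with maternal age, marital status, place of residence, and the condition of mother and neonate at discharge. The number of fetuses in the index pregnancy is not listed. Parity, number of children and number of previous pregnancies do not identify a twin index pregnancy.

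The comparison group is described twice. Methods/Design says: "Controls will be selected at random and balanced according to mode of delivery, maternal age and gestational age at the time of delivery". The Longitudinal component says the same: "Following a process of randomized selection balanced according to mode of delivery, maternal age and gestational age at the time of delivery". Plurality is not one of the three factors. Eligibility for controls is open to women "who have none of the conditions indicating severity will be eligible", and no sentence in the article limits cases or controls to singletons or mentions multiple pregnancy.

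Data analysis plans relative risks for adverse perinatal outcome and for "risk of impaired neuromotor and weight-height development in the children born from the pregnancy associated with severe maternal morbidity". Main hypotheses expects both to be worse after severe maternal morbidity.

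**The concern.** A confounder of the infant comparison is a factor that precedes severe morbidity, makes it more likely, and affects the infant by another route. Plurality is a plausible candidate on all three counts. It is fixed before the complication. It plausibly raises the risk of the hypertensive and hemorrhagic disorders in Appendix 2. It plausibly lowers birthweight and slows early growth whether or not the mother had a severe complication.

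Gestational-age balancing might be expected to deal with this, because twins are born earlier. It is not a dependable substitute. Among women without severe morbidity, those who deliver preterm are likely to include more twin pregnancies than those who deliver at term. Raising the preterm share of the controls to match the cases therefore also raises their twin share, by an amount that need not equal the twin share of the cases. Part of any relative risk for perinatal outcome, growth or development could then reflect plurality and not maternal morbidity.

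**Working it through.** **No figure to reproduce.** The article gives no sample size, event rate or effect for the infant comparison. Its one sample-size calculation (75,000 × 8/1000 = 600 near misses) belongs to the cross-sectional component. Every input below is an assumption.

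**Model, with no true effect of morbidity on the infant**

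- t = twin share of pregnancies without severe morbidity; OR = odds ratio of severe morbidity, twin against singleton.
- s0, t0 = preterm share without morbidity (singleton, twin); s1, t1 = the same with morbidity.
- k = ratio of infant-outcome risk, twin against singleton.
- Twin share of cases: c = o/(1+o), with o = OR × t/(1−t).
- Twin share of balanced controls: b = P × (twin share of preterm controls) + (1−P) × (twin share of term controls), where P = c·t1 + (1−c)·s1 is the preterm share of cases.
- If both twins are counted, a pregnancy share p becomes an infant share q = 2p/(1+p).
- Spurious RR = [1 + q_case(k−1)] / [1 + q_control(k−1)].

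**One case in full:** t = 2%, OR = 2, s0/t0 = 8%/50%, s1/t1 = 40%/70%, k = 2.

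- o = 2 × 0.02/0.98 = 0.0408, so c = 0.0392.
- P = 0.0392 × 0.70 + 0.9608 × 0.40 = 0.412.
- Twin share of preterm controls = 0.0100/(0.0100 + 0.0784) = 0.113; of term controls = 0.0100/(0.0100 + 0.9016) = 0.011.
- b = 0.412 × 0.113 + 0.588 × 0.011 = 0.053.
- Infant shares: cases 0.0755, unbalanced controls 0.0392, balanced controls 0.1007.
- RR without balancing = 1.0755/1.0392 = 1.03; with balancing = 1.0755/1.1007 = 0.98.
- If one infant per pregnancy is counted, these become 1.0392/1.0200 = 1.02 and 1.0392/1.0530 = 0.99.

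**Four cases** (t = 2%, s0/t0 = 8%/50%, k = 2, both twins counted)

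| OR | s1/t1 | Twin pregnancies: cases | Unbalanced controls | Balanced controls | RR unbalanced | RR balanced |
|---|---|---|---|---|---|---|
| 1.5 | 40%/60% | 3.0% | 2.0% | 5.2% | 1.02 | 0.96 |
| 2 | 40%/70% | 3.9% | 2.0% | 5.3% | 1.03 | 0.98 |
| 3 | 40%/70% | 5.8% | 2.0% | 5.4% | 1.07 | 1.01 |
| 4 | 30%/60% | 7.5% | 2.0% | 4.4% | 1.10 | 1.05 |

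**Grid.** t 1, 1.5, 2%; OR 1.5, 2, 3, 4; s0 6, 8, 10%; t0 40, 50, 60%; s1 20, 30, 40, 50%; t1 50, 60, 70, 80%, never below t0; k 1.5, 2, 3. This gives 4,752 combinations.

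- Without balancing: RR 1.005 to 1.19, always above 1.
- With preterm/term balancing: RR 0.84 to 1.16. It lies within 5% of 1 in 84% of combinations and within 3% in 67%.
- One infant per pregnancy, with balancing: RR 0.90 to 1.09, within 5% of 1 in 96%.
- Balanced controls have more twins than cases in 49% of combinations: 94%, 68%, 27% and 7% at OR 1.5, 2, 3 and 4.

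**Sensitivity to the preterm share of cases.** A second set of inputs takes 2% twin pregnancies, severe morbidity in 5% of singleton and 10, 15 or 20% of twin pregnancies, infant-outcome risk 10% against 30%, and s0/t0 = 7%/55%.

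- Unbalanced: 1.07, 1.14, 1.20.
- Balanced, cases 35%/65% preterm: 0.96, 1.02, 1.08.
- Balanced, cases 20%/60% preterm: 1.01, 1.07, 1.13.

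The direction changes with an input that the documents do not give. If the twin shares are equal in the two groups, as within strata of plurality, the spurious RR is 1.00.

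**The case against.** The strongest reply has four parts.

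1. **The distortion is small.** Under the planned balancing it is usually a few percent, and the larger upward values without balancing describe a design that is not planned. This stands, and it limits the weight of the point.

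2. **The article is condensed.** The list is not declared exhaustive and Data analysis ties it to no model. The case form collects obstetric characteristics, so a plurality field may already exist. This stands in part. It would lower the cost of the change, but it would not mend a list that goes down to the sex of the neonate and leaves out plurality. Balancing is also applied when controls are recruited, so an analysis plan cannot add a factor to it afterwards.

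3. **The model is simpler than the design.** It reduces gestational age to preterm or term and ignores balancing on mode of delivery and maternal age. It also ignores that controls are "randomly selected externally in a proportion of 1:1 from postpartum women in the rooming-in wards", which could change the twin share among preterm controls. This stands. The figures show plausible size and uncertain sign; they are not a prediction.

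4. **Stronger readings go beyond the text.** A reader might infer that balancing reverses the bias. The arithmetic shows only that it can: the result depends on the assumed odds ratio and on the preterm share of cases. A reader might also infer from "risk of impaired neuromotor and weight-height development in the children born from the pregnancy" that each twin counts as an independent child with double weight. That plural can simply be collective across women, and the definitions of neuromotor and weight-height development speak of one child per index pregnancy. The article does not settle how multiples are counted. That rule, and any clustering by mother, may properly sit in the full protocol or analysis plan.

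**Conclusion.** The point holds as an omission from a stated list and a stated set of balancing factors. The infant relative risks can be confounded by plurality, and balancing on gestational age cannot be relied on to remove it. The documents do not show that the comparison is in fact confounded, or in which direction, because they contain no twin, preterm or infant-outcome rates. Under the assumed inputs the spurious relative risk after balancing is usually within a few percent of 1, with extremes of about 0.84 and 1.16. This would matter mainly if a true effect on infant growth or development were itself small. It is a modest weakness in a main hypothesis, and cheap to correct.

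**What to change.** Add number of fetuses (singleton/multiple) to the control variables. State in Data analysis that the relative risks for perinatal outcome, neuromotor development and weight-height development are adjusted for plurality or stratified by it, with a singleton-only analysis as a sensitivity analysis. Recruitment need not change, since adjustment or stratification is enough. Keeping singletons as the sensitivity analysis avoids dropping twin infants from the main result.

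The cost is one chart field for cases and controls if it is not already collected, a sentence or two of analysis text, and slightly less precision.
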